## Abstract

**Background:**

Neuromuscular dysfunction is common in older adults and more pronounced in neurodegenerative diseases. In Parkinson's disease (PD), a complex set of factors often prevents the effective performance of activities of daily living that require intact and simultaneous performance of the motor and cognitive tasks.

**Methods:**

The cross-sectional study includes a multifactorial mixed-measure design. Between-subject factor grouping the sample will be Parkinson’s Disease (early PD vs. healthy). The within-subject factors will be the task complexity (single- vs. dual-task) in each motor activity, i.e., overground walking, semi-tandem stance, and isometric knee extension, and a walking condition (wide vs. narrow lane) will be implemented for the overground walking activity only. To study dual-task (DT) effects, in each motor activity participants will be given a secondary cognitive task, i.e., a visual discrimination task for the overground walking, an attention task for the semi-tandem, and mental arithmetic for the isometric extension. Analyses of DT effects and underlying neuronal correlates will focus on both gait and cognitive performance where applicable. Based on an a priori sample size calculation, a total N = 42 older adults (55–75 years) will be recruited. Disease-specific changes such as laterality in motor unit behavior and cortical control of movement will be studied with high-density surface electromyography and electroencephalography during static and dynamic motor activities, together with whole-body kinematics.

**Discussion:**

This study will be one of the first to holistically address early PD neurophysiological and neuromuscular patterns in an ecologically valid environment under cognitive-motor DT conditions of different complexities. The outcomes of the study aim to identify the biomarker for early PD either at the electrophysiological, muscular or kinematic level or in the communication between these systems.

**Clinical Trial Registration:**

ClinicalTrials.Gov,
NCT05477654. This study was approved by the Medical Ethical Committee (106/2021).

## Introduction

Parkinson’s disease (PD) is the second most common neurodegenerative disease after Alzheimer’s disease, affecting 2–3% of the population over 65 years of age worldwide
^
1,
2
^. This progressive disorder results from the depletion of dopaminergic neurons in the substantia nigra pars compacta
^
3
^. In the early stages of the disease, people with PD present mainly with motor symptoms such as tremor at rest, rigidity, bradykinesia, postural instability, and gait disturbances, which become more complex in advanced stages and are accompanied by non-motor symptoms
^
4
^. Clinically, the most striking features of people with postural instability/gait disorder (PIGD) are postural instability with falls and freezing of gait (FOG), which occur mainly in advanced stages and are episodic and unpredictable
^
5,
6
^. Gait impairments in people with PD encompass reduced speed and stride length, increased double limb support time, and stride-to-stride variability
^
7–
10
^.

Although PD motor symptoms dominate clinical presentations, most people with PD also experience cognitive and behavioral impairments, cognitive executive deficits, and depression
^
11,
12
^. The cognitive dysfunction observed in people with PD is primarily due to dopaminergic and cholinergic dysfunction
^
13
^, and is typically associated with impaired frontostriatal circuitry
^
11,
14
^, which impairs action planning and problem-solving
^
14
^, attentional set-shifting
^
15
^, response inhibition
^
16
^, and decision making
^
17
^. The three nonmotor frontostriatal circuits that connect frontal cortical regions to subcortical regions such as the basal ganglia originate in the dorsolateral prefrontal cortex (DLPFC), anterior cingulate cortex (ACC), and orbitofrontal cortex (OFC)
^
18
^.

A link between global cognitive dysfunction and motor symptoms in people with PIGD has been previously suggested
^
18
^. Compared to people who express tremor-dominant (TD) disease characteristics, people with PIGD have greater impairments on measures of global cognition
^
19
^, a higher frequency of mild cognitive impairment
^
20
^, and an increased risk of developing dementia
^
21
^. In their study of 783 participants, Kelly and colleagues
^
19
^ found an association between deficits in global cognition, executive function, memory, phonemic fluency, and more severe symptoms of postural instability/gait disturbance. While visuospatial impairments were associated only with more severe freezing and poorer memory function was associated only with greater postural instability, executive function deficits were associated with greater postural instability, more severe freezing, and gait impairments. Interestingly, gait characteristics of speed, variability, and postural control were also found to precede and predict declines in attention and visual memory
^
22,
23
^, as well as dementia in old age
^
24
^.

To understand the complexity of PIGD, locomotion control has been studied extensively. To efficiently perform a locomotor task, one should be able to (i) generate proper force for the step, (ii) maintain postural balance, and (iii) continuously adapt to environmental demands and behavioral goals
^
25
^. To ensure optimal walking, multiple sensorimotor processes must be functionally integrated on several levels to maintain the forward propulsion of the centre of mass while maintaining dynamic stability
^
26
^. At the highest level, the timing of muscle contraction between agonists, antagonists, and synergists acting on both sides of the body are precisely regulated
^
26
^. At lower levels, the behavior of motor units (MU) pattern is regulated following a size principle to ensure smooth muscle contractions
^
27
^. However, sensorimotor processes are impaired in people with PD, resulting in altered motor activity patterns during rest and locomotion
^
26
^. Moreover, it has been shown that the simultaneous performance of cognitive and motor tasks can increase differences in motor performance between healthy individuals and people with PD
^
26
^.

In daily life, balancing or walking is rarely the only task performed at a given moment (single task; ST). Most often, it is performed together with another task (dual task; DT) or sometimes even several other tasks as a multitasking activity, resulting in competition for limited resources which can degrade performance on one or all tasks
^
28
^. In case of performing cognitive and motor tasks simultaneously, the performance decrements are a consequence of cognitive-motor interference (CMI). By comparing the performance success of both, ST and DT conditions, we can calculate dual-task costs (DTC) using the following formula:
*(DT performance – ST performance) / ST performance*
^
29–
32
^. In people with PD, performing a cognitive serial subtraction task has been shown to impair the concurrently performed motor task as observed in decreased accuracy of force tracking
^
33
^, and promote deteriorating effects on the motor system such as inducing tremor
^
34
^. Studies of postural stability have shown that individuals with PD have impaired postural control under dual-task conditions
^
35,
36
^. Impaired walking in people suffering from PD is more pronounced under cognitive-motor DT conditions
^
37–
42
^, with additional impairments observed in symmetry and coordination between the left and right steps
^
43,
44
^. Walking difficulties in people with PD can additionally be exacerbated in situations where the walking path is being restricted, such as narrow pathways/corridors/doorways or when walking between objects
^
45
^. For example, Cowie and colleagues
^
46
^ have shown that people with PD slow down at doorways to an extent that is inversely proportional to doorway width and that the frequency of freeze events increases in narrower doorways.

Another important aspect is the cognitive effort involved in activities of daily living, which varies according to the complexity of the situation and the associated cognitive demands
^
47
^. Regardless of complexity, cognitive processing is highly dependent on visual information, ranging from the simplest scenario, such as recognizing and responding to a red light, to a highly complex scenario involving navigating through an unfamiliar city on uneven surfaces while ensuring the safety of the accompanying infant. These situations illustrate the importance of visual information processing for the generation, execution, and adaptation of motor commands during walking
^
48–
50
^.

People with PD experience walking difficulties and gait disturbances under the ST walking condition compared to healthy individuals, which become further exacerbated under the DT condition. Despite many efforts, it remains unclear how motor and cognitive symptoms contribute to ST or DT walking difficulties
^
29
^. Investigating the interaction between motor and cognitive symptoms not only on behavioral and but also on neurophysiological levels in ecologically valid settings could greatly enhance our understanding of the underlying mechanism of ST and DT performance decline. Such investigations, however, have only recently been enabled by the Mobile Brain/Body Imaging (MoBI;
^
51–
53
^) approach. which will be used in the present study to investigate time-synchronized electroencephalographic (EEG) and electromyographic (EMG) recordings as well as body movements in multilevel approach to understanding cognitive-motor interactions and their neuromuscular signature. The aim of the present study is to investigate the early PD disease-specific changes and laterality of neuronal rhythms during the three motor activities that demand different levels of cognitive-motor resources, namely (1) overground walking (dynamic condition), (2) semi-tandem stance (standing static condition), and (3) sustained isometric contraction (seated static condition), each as motor ST but also in combination with certain cognitive tasks in DT conditions. This will allow systematic assessment and identification of motor and cognitive factors contributing to the symptomatology of PD.

Compared with healthy participants, we hypothesize that early PD will have poorer ST performance on cognitive and motor tasks and increased DT costs on all motor activities. Furthermore, we expect that performance impairments with increased neural recruitment will be most pronounced in the highest motor complexity condition (walking in the narrow pathway) and even more pronounced in the corresponding DT variant (DT -narrow).

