### Outcome measures

This protocol focuses on the behavioral, cognitive, motor, and/or kinematic outcomes as well as neurophysiological markers associated with CMI during dual-tasking in healthy aged individuals and people with early PD. The accompanying information regarding the participants' demographics and general health will be treated as supporting outcome and used to control for the confounds.

**
*Principal outcomes*.** The principal outcomes suggested by this protocol will be the DT effects associated with the concurrent execution of overground walking/semi-tandem stance/isometric contraction
*and* a respective secondary cognitive task. The motor task parameters, e.g., the gait parameters using full-body kinematics (step length and width, stride time variability, walking speed), the center of pressure (COP) displacement for the static stance, and deviation of the required force development over time for the isometric contractions, will be investigated in the ST and DT conditions. Additionally, each cognitive task performance will be recorded in the ST condition to allow for the investigation of the DT effect on the cognitive level too. The cognitive ST condition will be performed in a seated position for all cognitive tasks (visual discrimination task, counting of Stroop stimuli, serial-3 subtraction; for description see below). High-density surface electromyography (HD-EMG) and high-density electroencephalography (HD-EEG) will be recorded in all motor activities in both ST and DT conditions. In the overground walking experiment, the DT condition will be created using a visual discrimination task, in the semi-tandem stance experiment the cognitive secondary task will be counting the occurrences of specific visual Stroop stimuli, and finally, in the isometric contraction experiment, the secondary task will encompass mental arithmetic. All tasks include aspects of executive functions. However, to avoid learning effects the task-set up was conducted differently between all conditions. Below are detailed descriptions of the cognitive and motor tasks. 

*Cognitive task performance:*

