Contra- vs. Ipsi-Lateral Visual Discrimination Task performance in walking activity: The outcome measures for a visual discrimination task will be response accuracy and response time. The implementation of such a task will allow for the recording of the event-related potentials as well as continuous brain activity. Stimuli of the cognitive task used in the ST and DT walking experiment will vary according to the presentation side (left vs. right), spectral properties (magenta vs. cyan), and presentation-response laterality (ipsi- vs. contra-lateral). DT costs and the associated neural underpinnings will be assessed in the cognitive task as well as in gait parameters.Silent counting of specific Stroop stimulus occurrences in the semi-tandem stance activity: Computerized Stroop task words “Blue” and “Red” will be presented one at a time in either blue or red ink color. Presenting stimuli at a rate of 1/s, participants will have to count the number of specific occurrences, e.g., “Blue” in blue ink, from the four possible options across 30-second intervals. This will be repeated three times, each time focusing on and counting a different color combination of stimuli.Mental arithmetic: Sequential subtracting is typically used as a screening procedure to assess attention/working memory functions. In our study, participants will be asked to quietly perform serial-3 subtraction from a random 3-digit number and verbally indicate the resulting number after a 30-second interval. This will be performed 3 times. The resulting number will be noted and will serve as an indirect measure of success. Standardization and adult norms are available
^
58
^.

*Motor performance:*

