### Statistical analysis and power calculation

Descriptive data will be presented as means (M) and standard deviations (SD). The homogeneity of variances and normality of distribution of parameters will be tested with Levene's test and Shapiro-Wilk test, respectively. Using univariate analyses of variances (ANOVA), the between-subject factor grouping the sample will be
*PD* (early PD vs. no PD), while the within-subject factors will be the
*task complexity* (ST vs. DT) in each motor activity, i.e., the overground walking, semi-tandem stance, and isometric force knee extension, as well as the
*walking condition* (wide vs. narrow) for the overground walking only. Significance will be set at alpha = 0.05. The effect size will be presented as the unbiased adjusted partial eta squared
^
78
^. All post-hoc comparisons will control for multiple comparisons (e.g., Bonferroni). Statistical analyses will be done using SPSS (IBM, SPSS Inc, Chicago, IL, United States) or R (R Core Team, 2013).

Sample size estimation calculated using g*Power software (a priori: F-tests; ANOVA: repeated measures, within-between interaction; effect size f = 0.2; alpha error probability = 0.05; power (1-beta error probability) = 0.8; number of groups = 2; number of measurements = 3) revealed a total of
*N* = 42 subjects, half of who will be healthy older adults, and the other half will encompass people with early-stage PD.

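### The dual-task cost hypothesis is proportional, but the only model stated for it tests absolute change; the two can disagree when the groups differ at single task, as the protocol expects

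*Protocol article*

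**What the plan says.** - **Definition.** The Introduction of the protocol article says "we can calculate dual-task costs (DTC) using the following formula" and gives DT minus ST divided by ST: "DT performance – ST performance) / ST performance".
- **Hypothesis.** The end of the Introduction expects that "early PD will have poorer ST performance on cognitive and motor tasks and increased DT costs on all motor activities". One sentence thus predicts an ST difference and a cost difference. A second hypothesis expects impairment to be greatest on the narrow path, and more so in its DT variant.
- **Outcomes.** Under Outcome measures: "The principal outcomes suggested by this protocol will be the DT effects associated with the concurrent execution of overground walking/semi-tandem stance/isometric contraction", combined with a cognitive task. No scale is given for these effects. For the walking activity the same section adds: "DT costs and the associated neural underpinnings will be assessed in the cognitive task as well as in gait parameters". No test is named.
- **Analysis.** Statistical analysis and power calculation says: "Using univariate analyses of variances (ANOVA), the between-subject factor grouping the sample will be" PD status, with a within-subject factor of task complexity ("ST vs. DT) in each motor activity") and, for walking only, wide vs. narrow. "Significance will be set at alpha = 0.05". Trial design describes the same 2 x 2 and 2 x 2 x 2 layouts, and the sample size is based on the within-between interaction.

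**The concern.** The cost merges ST and DT into one value per person. It therefore cannot be the dependent variable in a model that has ST vs. DT as a factor. In that model the dependent variable is performance, and the Group x task interaction compares the mean of DT minus ST between groups.

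That matches the cost hypothesis only if the groups start from the same ST level, and the protocol predicts that they do not. A significant interaction could then be reported as a higher DT cost in PD when the proportional costs are equal. For outcomes where higher is better, a truly higher proportional cost could be hidden or appear reversed.

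The formula's sign adds ambiguity. A deterioration gives a negative value for speed, step length and accuracy, and a positive value for sway and response time. An increased cost across all activities therefore has no single direction.

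**Working it through.** **1. The plan's own figure.** Inputs from Statistical analysis and power calculation: f = 0.2, alpha 0.05, power 0.8, 2 groups, 3 measurements. The correlation between measurements is not given, so 0.5 is assumed. Noncentrality = f² x N x m / (1 − rho) = 0.04 x 42 x 3 / 0.5 = 10.08, with 2 and 80 degrees of freedom. Power is 0.803, so N = 42 reproduces. The figure is for the within-between interaction, not for a test on the cost.

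**2. The two null hypotheses.** Let S be the mean ST level and c the mean proportional cost in a group, with cost unrelated to ST level within the group. The mean absolute change is S x c.
- Interaction null: S_PD x c_PD = S_H x c_H.
- Cost null: c_PD = c_H.

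They coincide only if S_PD = S_H or both costs are zero.

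**3. Direction by type of outcome** (illustrative values; the protocol gives no means or SDs).
- Speed, equal cost of −15%, ST 1.2 vs. 0.96 m/s: changes of −0.180 and −0.144 m/s. PD appears less affected.
- Sway, equal cost of +20%, ST 30 vs. 42 cm: changes of +6.0 and +8.4 cm. PD appears more affected.
- Conversely, an equal absolute change of −0.18 m/s from 1.2 and 0.96 m/s: costs of −15.0% and −18.75%. The interaction is null while the costs differ.

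**4. How often this matters.** In a 2 x 2 mixed ANOVA the interaction test is the two-sample t-test on DT minus ST. Simulation, 20,000 runs per setting: log-normal outcome where higher is worse, 21 per group, equal 20% cost, between-person CV 25%, within-person CV 8% or 12% (all assumed). Entries are the percentage of studies significant at 0.05.

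| PD worse at ST by | Interaction, within CV 12% | Interaction, within CV 8% | Test on cost or log ratio |
|---|---|---|---|
| 0% | 5 | 5 | 5 |
| 10% | 6 | 7 | 5 |
| 20% | 9 | 13 | 5 |
| 30% | 13 | 22 | 5 |
| 50% | 24 | 43–44 | 5 |

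**5. A second set of assumptions** (normal ST values, cost varying between people, 21 per group).
- Speed: healthy ST 1.2 m/s, CV 15%, cost −15% in both groups, SD of cost 8 points. With PD at 100/90/80/70% of healthy ST speed, the interaction rejects in 5/9/24/50% of runs. Where ST differs, nearly all rejections point to a smaller loss in PD.
- Sway: healthy ST 30 cm, CV 25%, cost +20% in both groups, SD of cost 12 points. With PD at 1.0/1.2/1.4/1.6 times healthy, it rejects in 5/13/34/57% of runs. Where ST differs, nearly all point to a larger change in PD.
- Power for speed: true costs −10% healthy and −15% PD, CV 15%, SD of cost 6 points. With PD at 100/90/80/70% of healthy ST speed, interaction power is 71/45/20/6%. The test on the cost keeps about 75%.

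**The case against.** - **The scale is inferred.** The analysis section does not say that the ANOVA uses untransformed values. It plans Levene and Shapiro-Wilk tests without saying what follows if they fail, so a transformation is possible. Such detail is often left to a fuller document. This stands as a limit on certainty. But the definition, the hypothesis and the model are all in the article, and followed as written they do not match.
- **The cost formula sits in the background.** It appears in the Introduction, the principal outcome speaks only of DT effects, and an assessment of DT costs is announced for walking. This is fair, but the announcement names no test, and the hypothesis uses the term that the formula defines.
- **A reader might infer that the ANOVA fails the study's hypotheses altogether.** The documents do not support that. The factorial model addresses the ST comparison and the wide/narrow gradient directly. Only the cost clause is exposed.
- **A reader might infer that false-positive rates of 20–40% are to be expected.** The protocol gives no size for the ST difference. Eligibility limits PD to Hoehn and Yahr 1–2, disease under 5 years and SPPB above 7. The 30% and 50% rows are the severe end for such a sample, and at 10% the excess is small.
- **A reader might infer that a log-scale model is the one right analysis.** It is not. Its interaction is a ratio of geometric means rather than the protocol's mean cost, and it does not suit accuracy or counts. The protocol's own cost measure is available.

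**Conclusion.** The point holds for the increased-cost hypothesis. The protocol predicts a difference in a proportional measure together with a difference in its denominator, and states only a model whose interaction, with no transformation stated, tests absolute change. The mismatch can create an apparent effect for sway, response time, variability and force deviation, and can mask or reverse one for speed and step length.

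Under the main assumptions (equal 20% cost, between-person CV 25%, within-person CV 8–12%, 21 per group), the chance of a significant interaction is about 6–7% at a 10% ST difference, 9–13% at 20%, 13–22% at 30% and 24–44% at 50%, against a nominal 5%. That the null hypotheses differ follows from the algebra. The rates depend on assumed inputs, above all on the ST difference, which the protocol does not quantify.

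**What to change.** 1. For the increased-cost hypothesis, state as the test a between-group comparison of the cost already defined in the Introduction. For walking, use Group x wide/narrow with the cost as dependent variable. For positive continuous outcomes, Group x task on log values is an acceptable equivalent.
2. Orient the sign for each outcome so that a positive cost always means worse performance under dual task.
3. Keep the Group x task ANOVA on untransformed values for the ST and walking-condition hypotheses, and as supportive evidence on absolute change.

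The cost is one extra analysis and some wording; cost results then read as proportions rather than units. No new data are needed. Study status reports 6 participants tested, so the choice could be fixed while most of the data are still to be collected.
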